### Endpoints

The primary endpoint is the proportion of patients with pTRG3, which is determined postoperatively by each sub-center and verified by the primary center.

The secondary endpoints include (1) the proportion of patients with TRG on MRI (mrTRG) (1–5) after 2 cycles/4 cycles of CAPOX; (2) the proportion of patients with pTRG (0–2); (3) survival prognosis of patients with different pTRG, containing disease-free survival (DFS), local recurrence rate (LR), distant recurrence rate (DR), and overall survival (OS); (4) 3-year DFS and OS of patients with different pTRG; (5) the predicted imaging indicators of pTRG; (6) the accuracy of pTRG judged by imaging; (7) the adverse effects of chemotherapy; (8) the incidence of perioperative complications; and (9) the QOL of patients during chemotherapy and after surgery.

### Sample size calculation

According to phase II trial [16], the proportion of patients who had poor pathological remission (pTRG 3) after 4 cycles of CAPOX was 27.9%. The proportion of pTRG3 after 2 cycles of CAPOX is expected to increase by no more than 10%. The non-inferiority test is used with *α* = 0.05, (1-β) = 0.8, and the non-inferiority margin (hazard ratio) value δ is set as 0.05. Pearson chi-square test is used to calculate the sample size required for the experiment, and 249 samples are required for each group calculated by a normal approximation algorithm [25]. Ten percent of patients are estimated to withdraw from the group or lost to follow-up; 277 patients are needed in each group. The planned enrollment time is 2.5 years, and the total number of patients is about 554 cases. Meanwhile, it is assumed that the dropout rate of patients in the 4 cycles of the CAPOX group is about 6% due to intolerance of chemotherapy. Therefore, it is estimated that 294 patients would be included in the 2 cycles of the CAPOX group and 260 patients in the 4 cycles of the CAPOX group.

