### Randomization and intervention

Each sub-center will be responsible for potential enrollment and consent-taking. Central randomization will be performed as soon as the enrollment is determined using the central automated randomization system offered by the O-trial online system (https://plus.o-trial.com/). Sub-center will upload the information of eligible patients on the O-trial system, which will sequentially number and randomize the uploaded patients into 2 or 4 cycles of CAPOX in a 1:1 ratio automatically. No stratification is included in the current study.

Patents in both groups will undergo TME surgery after 2 or 4 of CAPOX. Each cycle of CAPOX includes oxaliplatin 130 mg/m^2^, once daily on day 1, every 21 days and capecitabine 1000 mg/m^2^, twice daily on days 1 to 14, every 21 days. TME surgery was performed by experienced colorectal surgeons 2–3 weeks after the last cycle of preoperative CAPOX.

Postoperative adjuvant treatment will be performed according to the ESMO and Chinese guidelines for colorectal cancer [19, 20]. Based on the pathological stage, patients with a positive CRM or N2 stage would be recommended to undergo postoperative radiotherapy. Adjuvant chemotherapy was recommended for N + patients. The long-term survival of the patients will be followed up.

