At present, there are retrospective and small prospective studies [27, 28, 32, 34, 36] that have shown that chemotherapy alone could still achieve an excellent prognosis for low- and intermediate-risk stage II/III rectal cancer, and there are also large RCTs that are validating whether neoadjuvant chemotherapy alone non-inferior to neoadjuvant chemoradiotherapy for low-risk stage II/III rectal cancer [37]. Although the results have not yet been announced, it is speculated from the existing evidence that NCT alone can achieve relatively good results for patients with low- and intermediate-risk. However, the evaluation time of chemotherapy effects in previous studies was 12 weeks after chemotherapy (6 cycles of FOLFOX or 4 cycles of CAPOX), which was relatively long. Patients who are not sensitive to chemotherapy may need to convert to surgery, radiotherapy, and other intensive treatments in advance, and the relatively long-term chemotherapy may lead to delay of patients’ opportunity to receive necessary treatment, causing a series of oncology consequences and acquiring unnecessary adverse effects of chemotherapy.

The power of the COPEC trial lies in its 2 verse 4 cycles’ design to acquire early pathological outcomes after NCT. Based on our previous phase II study, we hypothesize COPEC trial could obtain a good pathological response judgment in patients with low- and intermediate-risk stage II/III rectal cancer after 2 cycles of preoperative CAPOX chemotherapy. The major challenge of the COPEC trial is the difficulty in patient enrollment, which is mainly due to the worry that 2-cycle CAPOX maybe not be powerful enough in dealing with local advanced rectal cancer. However, we have proved in the previous phase II study that obvious tumor morphological changes were observed after 2 cycles of preoperative CAPOX chemotherapy and those who responded poorly after 2 cycles of NCT would not benefit from 2 more cycles. So perhaps, in the future, the follow-up standard treatment plan for patients with low- and intermediate-risk rectal cancer may become NCT alone without radiotherapy combined with early assessment of tumor response and screening out those with poor response to NCT for further advanced treatment. We hope the COPEC trial could help in establishing a consensus standard of low- and intermediate-risk rectal cancer and the early identification of stage II/III rectal patients with low- and intermediate-risk who are poorly responding to NCT.

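### The 249 per group and 80% power rest on two inputs that the sample size section does not state: no true difference between the arms, and a 10-point absolute margin

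*Protocol article*

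**What the plan says.** All the inputs are in the section Sample size calculation of the Protocol article.

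- Control rate: "the proportion of patients who had poor pathological remission (pTRG 3) after 4 cycles of CAPOX was 27.9" (percent), taken from the group's phase II trial.
- Two-cycle rate: "The proportion of pTRG3 after 2 cycles of CAPOX is expected to increase by no more than 10" (percent). No point value is given.
- Test: "The non-inferiority test is used with *α* = 0.05", with power 0.8. Whether alpha is one-sided or two-sided is not stated.
- Margin: "the non-inferiority margin (hazard ratio) value δ is set as 0.05".
- Result: "249 samples are required for each group calculated by a normal approximation algorithm".
- Inflation: "Ten percent of patients are estimated to withdraw from the group or lost to follow-up; 277 patients are needed in each group", for a total of about 554.

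The section Randomization and intervention says the system will "randomize the uploaded patients into 2 or 4 cycles of CAPOX in a 1:1 ratio automatically", so equal group sizes are the right basis for the calculation.

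**The concern.** A non-inferiority sample size needs two separate quantities: the true difference assumed for the power, and the largest difference that will be tolerated. This section gives one bound on an increase (10%) and one number labelled as the margin (0.05, called a hazard ratio although the endpoint is a proportion). It never says which true difference the power assumes. A reader who sees the sentence on an increase next to an unqualified 80% would conclude that the 249 allows for some loss of response with 2 cycles.

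If it allows for none, 80% is the power at the most favourable point of the 0 to 10 bound. A modest true loss, well within 10 points, could then lead to a missed non-inferiority result, and in a trial described as 80% powered that miss could be mistaken for evidence that 2 cycles are worse.

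**Working it through.** **Step 1: reproduce 249.** With rate p = 0.279 in both arms, margin M = 0.10, one-sided alpha 0.05 (z = 1.645) and power 0.8 (z = 0.842):

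n = (1.645 + 0.842)² × 2 × 0.279 × 0.721 / 0.10² = 248.7 with unrounded z values, rounded up to **249**.

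Dropout: 249 / 0.90 = 276.7, rounded up to 277; 2 × 277 = 554. Both match the section.

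**Step 2: try the other readings.** None of these gives 249.

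| Reading | n per group |
|---|---|
| Margin 0.10, no difference, one-sided 0.025 | 316 |
| Margin 0.05, no difference, one-sided 0.05 | 995 |
| Margin 0.05, no difference, one-sided 0.025 | 1264 |
| Superiority, 27.9% vs 37.9%, one-sided 0.05 (without / with continuity correction) | 272 / 292 |
| Superiority, 27.9% vs 37.9%, two-sided 0.05 (without / with continuity correction) | 346 / 366 |
| Margin 0.10, 2-cycle rate 30.69% (10% relative rise), one-sided 0.05 | 493 |
| Margin 0.10, 2-cycle rate 32.9%, one-sided 0.05 | 1044 |

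**Step 3: power at 249 per group when the true rise is d.**

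Power = Φ((M − d)/SE − 1.645), where SE = √[0.279 × 0.721/249 + (0.279 + d)(0.721 − d)/249].

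At d = 0, SE = 0.0402. With M = 0.10: Φ(0.10/0.0402 − 1.645) = Φ(0.84) = 80%. With M = 0.05: Φ(0.05/0.0402 − 1.645) = Φ(−0.40) = 34%.

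At d = 0.02, SE = 0.0406. With M = 0.10: Φ(0.08/0.0406 − 1.645) = Φ(0.32) = 63%. With M = 0.05: Φ(0.03/0.0406 − 1.645) = Φ(−0.91) = 18%.

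| True rise (points) | Power, M = 10 points | Power, M = 5 points (δ read as an absolute difference) |
|---|---|---|
| −1 | 86.6% | 44.3% |
| 0 | 80.0% | 34.4% |
| 1 | 72.0% | 25.6% |
| 2 | 62.7% | 18.2% |
| 3 | 52.8% | 12.4% |
| 4 | 42.8% | 8.1% |
| 5 | 33.4% | 5.0% |
| 10 | 5.0% | 0.2% |

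Simulation of the 10-point column (400,000 trials per row) gave 80.2%, 62.9% and 33.4% at rises of 0, 2 and 5 points.

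**Step 4: sensitivity to group sizes.** The section expects 294 and 260 patients in the 2-cycle and 4-cycle groups. After 10% loss that is about 265 and 234, and the power at rises of 2 and 5 points is unchanged (62.7% and 33.4%). If all 277 per group were evaluable, it would be 66.7% and 35.8%.

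**The case against.** The strongest reply is that one sentence cannot serve two purposes. If the 10% is the margin, the article states no expected rise, and a zero-difference assumption contradicts nothing. If the 10% is an expectation, the margin is the written 0.05 and the 10-point power figures do not apply. This is a fair constraint, and it rules out a reading that a reader might well adopt: that the plan itself predicts a rise and then ignores it. The sentence is an upper bound that includes zero, and 10 points is the very margin that reproduces 249.

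The dilemma does not clear the section, though. If 10% is the margin, the section labels a different number as the margin and gives no 2-cycle rate at all. If 10% is the expectation, power is about 34% even at equality, and rises up to twice the 5-point margin are contemplated.

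Next, designing at equality is common, and every such trial loses power when the truth is worse. The Discussion also gives grounds for equality: it argues that poor responders after 2 cycles gain nothing from 2 more. Both points stand. Assuming equality is defensible; leaving it unstated beside wording about an increase is the fault. For the same reason the Discussion's mention of "the worry that 2-cycle CAPOX maybe not be powerful enough in dealing with local advanced rectal cancer" should not be read as an effect assumption. It explains slow enrolment and is answered in the next sentence.

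Finally, an article may leave a power table, and wording on how to read a missed result, to the full protocol or analysis plan. That is true of the table. But this article reports the calculation itself, and the inputs it prints do not yield the result it prints.

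**Conclusion.** The point holds as a defect in how the calculation is stated. The 249 per group and 80% power require 27.9% in both arms, a 10-point absolute margin and one-sided alpha 0.05. The section states neither the equality nor that margin, and it prints δ = 0.05 instead. On the reproducing inputs, power falls to about 72%, 63%, 53% and 33% at true rises of 1, 2, 3 and 5 points. Those rises are illustrations chosen for this check, not figures from the article. The 34% and 18% for δ = 0.05 assume that it is an absolute difference; the hazard ratio label leaves the scale unclear.

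Three stronger inferences are not supported:

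- That 80% holds only if 2 cycles are exactly as good as 4. The condition is no worse; power is 87% if 2 cycles are 1 point better.
- That any real loss makes a miss likely. With a 10-point margin, success remains more likely than not up to 3 points (52.8%) and becomes the less likely outcome from about 4 points (42.8%).
- That a single average power over 0 to 10 points describes the trial. Nothing in the article supports an even weighting, and the range includes the margin itself, where power equals alpha by construction.

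**What to change.** Rewrite the paragraph in Sample size calculation so that it:

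1. states the assumed true 2-cycle pTRG3 rate separately from the tolerated margin;
2. reconciles the margin and its scale with δ = 0.05 and the hazard ratio label, and states that alpha is one-sided if it is;
3. gives the power as conditional. For a 10-point margin, suitable wording is:

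> With 249 evaluable patients per group, a 10-point absolute margin and one-sided alpha 0.05, power is at least 80% if the pTRG3 rate is 27.9% after 4 cycles and truly no higher after 2. Power is about 72%, 63%, 53% and 33% if the 2-cycle rate is truly 1, 2, 3 or 5 points higher (illustrative values).

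If 0.05 is kept as an absolute margin, the power to state at 249 per group is about 34% at equality and 18% at a 2-point rise;

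4. adds that a missed non-inferiority result is inconclusive unless the confidence interval excludes no difference.

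The cost is one paragraph and a less favourable power statement. No extra patients and no change of design are requested.

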### Data-analysis

The trial statistician, who will be blinded to randomization, will carry out the data analysis process. Before analysis, they will assess the integrity of collected data, and repeated or missing data will be described accordingly. Demographics and repeatedly measured clinical characteristics of participants will be summarized as the baseline.

SPSS for Windows, version 25 (IBM Corp, Armonk, NY), and GraphPad Prism for Windows, version 8.0.0 (GraphPad Software, San Diego, California), are used for data analysis. Continuous data are shown as the mean and standard deviation. Categorical variables are represented as percentages. Continuous variables are compared using the Mann–Whitney *U* test. Categorical variables are compared between groups using Fisher’s exact test or the chi-square test. Fisher’s exact test or the chi-square test is used to compare the proportions of patients with pTRG3, the proportion of patients with TRG on MRI (mrTRG) (1–5) after 2 cycles/4 cycles of CAPOX, and the proportion of patients with pTRG (0–2). Survival of patients (OS, DFS) is compared using Kaplan–Meier analysis. Statistical significance is defined as a *p*-value less than 0.05. Especially, in the 4 cycles of the CAPOX group, patients who receive less than 3 cycles of chemotherapy due to adverse effects or drop-out will be analyzed as the 2 cycles of the CAPOX group; others will be analyzed in the 4 cycles of the CAPOX group analysis.

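### The sidedness of α is not stated, 249 per group fits only a one-sided 5% test with a 10-point margin, and the pTRG3 analysis at p<0.05 carries over neither that level nor any margin

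*Protocol article*

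**What the plan says.** All references are to the protocol article.

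- **Sample size calculation, level and power:** "The non-inferiority test is used with *α* = 0.05, (1-β) = 0.8". Neither one-sided nor two-sided is written.
- **Sample size calculation, rates:** "the proportion of patients who had poor pathological remission (pTRG 3) after 4 cycles of CAPOX was 27.9" per cent, and "The proportion of pTRG3 after 2 cycles of CAPOX is expected to increase by no more than 10" per cent.
- **Sample size calculation, margin:** "the non-inferiority margin (hazard ratio) value δ is set as 0.05".
- **Sample size calculation, result:** "249 samples are required for each group calculated by a normal approximation algorithm", and then "Ten percent of patients are estimated to withdraw from the group or lost to follow-up; 277 patients are needed in each group".
- **Data-analysis, primary comparison:** "Fisher’s exact test or the chi-square test is used to compare the proportions of patients with pTRG3".
- **Data-analysis, threshold for all comparisons:** "Statistical significance is defined as a *p*-value less than 0.05".

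The Data-analysis section gives no margin, no confidence interval and no sidedness for pTRG3.

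**The concern.** A non-inferiority conclusion needs three things fixed together: a margin, a one-sided level (or the matching interval), and a rule that compares the interval with the margin. Here the level is written as 0.05 in both sections, but sidedness must be inferred. The inference differs between them: the sample size points to one-sided 5% (a 90% interval), while a chi-square or Fisher p-value below 0.05 is by convention two-sided (a 95% interval, or one-sided 2.5% for non-inferiority).

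Three things are at stake. Followed literally, the analysis rule tests equality and cannot show non-inferiority. An analyst who adds a margin but keeps the usual meaning of p<0.05 would use an interval for which the trial was not sized. And while the level is open, it could be settled after the data are seen.

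**Working it through.** **Inputs.** pTRG3 rate of 27.9% after 4 cycles, α = 0.05, power 0.80, an increase of at most 10 points, δ = 0.05, 249 per group, 10% loss (all from Sample size calculation). Equal true rates in the two arms are my assumption; the article does not state the true difference used.

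**1. Reproducing 249.** With equal rates and the unpooled normal approximation,

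n = (z₁₋α + z₀.₈)² × 2 × 0.279 × 0.721 / margin², where 2 × 0.279 × 0.721 = 0.40232.

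| Margin | One-sided α | (z₁₋α + z₀.₈)² | n per group |
|---|---|---|---|
| 0.10 | 0.05 | 6.1826 | 248.7 → **249** |
| 0.10 | 0.025 | 7.8489 | 315.8 → 316 |
| 0.05 | 0.05 | 6.1826 | 994.9 → 995 |
| 0.05 | 0.025 | 7.8489 | 1263.1 → 1264 |

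249/0.9 = 276.7, rounded up to the stated 277. Other constructions do not give 249. A difference test of 27.9% v 37.9% needs 272 one-sided or 346 two-sided. A true rate of 32.9% with a 10-point margin needs 1044 at one-sided 0.05. Of the constructions tried, only the first row of the table matches.

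**2. Power with 249 per group.** SE = √(0.40232/249) = 0.0402, and power = Φ(margin/SE − z₁₋α).

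- Margin 0.10: 0.10/0.0402 = 2.488. One-sided 0.05: Φ(2.488 − 1.645) = 80.0%. One-sided 0.025: Φ(2.488 − 1.960) = 70.1%.
- Margin 0.05: 0.05/0.0402 = 1.244. One-sided 0.05: Φ(1.244 − 1.645) = 34.4%. One-sided 0.025: Φ(1.244 − 1.960) = 23.7%.

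**3. Results that depend on the interval.** Take 70/249 events in the 4-cycle arm (28.1%, close to 27.9%), Wald limits and a 10-point margin.

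| 2-cycle events | Increase (points) | Upper limit, 90% CI | Upper limit, 95% CI |
|---|---|---|---|
| 75 | 2.0 | 8.70 | 9.99 |
| 76 | 2.4 | 9.12 | 10.40 |
| 77 | 2.8 | 9.53 | 10.82 |
| 78 | 3.2 | 9.95 | 11.24 |
| 79 | 3.6 | 10.36 | 11.65 |

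At 75 events both intervals pass and at 79 both fail. At 76 to 78 they disagree. If the arms are truly equal, the two rules disagree in about 80.0 − 70.1 = 9.9% of trials. At a true increase of exactly 10 points, non-inferiority is wrongly declared in 5% v 2.5% of trials.

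**4. The test as written.** For the same 76 to 78 v 70 events, the two-sided chi-square p (no continuity correction) runs from about 0.56 to 0.43, so it is far from 0.05 whichever side is used. It compares the rates with each other and not with a margin. With 249 per group its two-sided power to detect 27.9% v 37.9% is about 66%. In about 100 − 66 = 34% of trials it would therefore be non-significant although 2 cycles was truly worse by the full 10 points. A non-significant result would not show non-inferiority.

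**The case against.** A reader might infer that the article sets two different alpha levels for its primary decision, and that the power of its planned analysis is therefore 70% and not 80%. The article does not support that. Both sections give 0.05; no 0.025 level, no two-sided wording and no 95% interval rule appear. A non-inferiority test is directional, and a one-sided p<0.05 would satisfy both sections. The 70% belongs to a 95% interval set against a 10-point margin, a procedure that the article does not contain. It is not the power of the chi-square or Fisher comparison. The change of verdict at 76 to 78 events likewise arises between two interval rules, neither of them stated. All of this stands, so the power loss must be put conditionally.

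It is also fair to say that the margin is the larger problem. On the stated δ of 0.05 read as a risk difference, 249 per group falls well short of 80% power at either level. That stands too, and so the level and the margin have to be corrected together.

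A last objection is that sidedness and interval level belong in the full protocol or SAP, which are not shown. That would answer a mere omission. Here the article itself names the test, the threshold, the α and the sample size, and the named test cannot deliver the conclusion for which the sample size was calculated.

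**Conclusion.** The point holds in a limited form. The article leaves the sidedness of α unstated, and its 249 per group matches a one-sided 5% test with a 10-point margin and equal rates of 27.9%, not its stated δ. The primary analysis, as described, is a test of equality with no margin or interval level, so it neither tests non-inferiority nor carries over the level behind the sample size.

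The drop in power from 80.0% to 70.1%, and the band of observed increases from about 2.4 to 3.2 points whose verdict changes, apply only if the p<0.05 threshold is turned into a two-sided 95% interval. They also assume a 10-point margin, about 28% pTRG3 in the 4-cycle arm and 249 analysed per group; the power figures further assume no true difference. This should be corrected before analysis.

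**What to change.** In **Sample size calculation**, write one-sided α = 0.05. Reconcile δ = 0.05, labelled a hazard ratio although pTRG3 is a proportion, with the 10-point risk difference that reproduces 249, and state the assumption of equal true rates.

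In **Data-analysis**, replace the chi-square or Fisher decision for pTRG3 with this rule: non-inferiority is concluded if the upper limit of the two-sided 90% confidence interval for the risk difference (2 cycles minus 4 cycles) lies below that margin. Report the 95% interval beside it, and limit two-sided p<0.05 to the other comparisons.

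If the sponsor wants the 95% interval to decide, keep the enrolment and restate the power as about 70% at a 10-point margin; 80% would need 316 per group, or 316/0.9 = 352 with 10% loss.

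The cost is a few sentences, fixed before analysis, and no added patients. The price is a less flattering statement: either an openly one-sided 5% level or a power of about 70%.

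### The non-inferiority margin is printed as a hazard ratio of 0.05, which is not the margin behind 249 per group; read as 5 percentage points, that size gives about 34% power, not the stated 80%.

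*Protocol article*

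**What the plan says.** All the inputs stand in the Sample size calculation section of the protocol article, apart from the endpoint and the allocation.

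- Endpoint (Endpoints section): "The primary endpoint is the proportion of patients with pTRG3". This is a yes/no result read from the surgical specimen.
- Control rate, from the group's phase II study: "the proportion of patients who had poor pathological remission (pTRG 3) after 4 cycles of CAPOX was 27.9" per cent.
- Change anticipated with 2 cycles: "The proportion of pTRG3 after 2 cycles of CAPOX is expected to increase by no more than 10" per cent.
- Error rates: "The non-inferiority test is used with *α* = 0.05", with power 0.8. The section does not say whether alpha is one-sided.
- Margin: "the non-inferiority margin (hazard ratio) value δ is set as 0.05".
- Result: "249 samples are required for each group calculated by a normal approximation algorithm".
- Inflation: "Ten percent of patients are estimated to withdraw from the group or lost to follow-up; 277 patients are needed in each group".
- Allocation (Randomization and intervention): the system will "randomize the uploaded patients into 2 or 4 cycles of CAPOX in a 1:1 ratio automatically".

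No other section states a margin or corrects this one.

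**The concern.** There are two separate difficulties. First, the scale. A hazard ratio compares event rates over time, and pTRG3 has no time to event. Even as a ratio, 0.05 could not serve as a limit on how much worse 2 cycles may be, since a ratio margin of that kind would lie above 1.

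Second, the size. The natural rescue is to read 0.05 as an absolute difference of 5 percentage points. The same section, however, allows for a rise in pTRG3 of up to 10%, twice that margin if the 10% is absolute. A trial cannot be planned to show a difference below 5 points while allowing that the true difference may be 10.

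In a non-inferiority trial the margin is the success criterion. If the published plan supports two margins, the same data can be declared non-inferior or not. A margin chosen once the results are known would void the conclusion.

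**Working it through.** **Inputs.** Control rate p = 0.279, power 0.80, alpha 0.05 and 1:1 allocation, all from the article. Two inputs are not stated and are assumed: equal true rates in both arms, and a one-sided alpha. They are chosen because together they reproduce the plan's own figure.

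**Formula.** Normal approximation for non-inferiority of two proportions, per group:

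n = (z₁₋α + z₀.₈₀)² × 2p(1 − p) / δ²

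Here 2p(1 − p) = 2 × 0.279 × 0.721 = 0.4023. For one-sided 0.05, (1.645 + 0.842)² = 6.183. For one-sided 0.025, (1.960 + 0.842)² = 7.849.

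**Step 1: reproduce 249.** With δ = 0.10 and one-sided 0.05, n = 6.183 × 0.4023 / 0.01 = 248.7, rounded up to 249. Then 249 / 0.90 = 276.7, rounded up to 277, the next figure in the plan. Solving the formula backwards for n = 249 gives δ = 0.0999.

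**Step 2: use the printed 0.05 as a risk difference.** n = 6.183 × 0.4023 / 0.0025 = 994.9, so 995 per group, four times the plan's figure.

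**Step 3: power at 249 per group.** The standard error of the difference is √(0.4023 / 249) = 0.0402, and power = Φ(δ / 0.0402 − z₁₋α).

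| Margin | One-sided alpha | Power at 249 per group | n per group for 80% |
|---|---|---|---|
| 0.10 | 0.05 | 80.0% | 249 |
| 0.10 | 0.025 | 70.1% | 316 |
| 0.05 | 0.05 | 34.4% | 995 |
| 0.05 | 0.025 | 23.7% | 1,264 |

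With a 5-point margin and one-sided 0.05, counting all 277 per group as evaluable raises power only to 37.0%. The 294/260 split at the end of the section gives 36.9%.

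**Step 4: look for another reading that gives 249 with 0.05.**

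- 2-cycle rate 5 or 10 points higher (32.9% or 37.9%): no sample size exists, because the assumed difference meets or exceeds the margin.
- 2-cycle rate 10% higher in relative terms (30.7%): more than 5,000 per group.
- Ordinary chi-square comparison of 27.9% with 37.9%: 272 one-sided or 346 two-sided; 292 or 366 with continuity correction.
- Risk-ratio margin of 1.05: about 13,400 per group. A literal ratio of 0.05: about 4 per group.

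**Step 5: effect on the verdict.** At one-sided 5% the upper confidence limit lies 1.645 × 4.02 = 6.6 points above the observed difference (2 cycles minus 4 cycles). Success at a 10-point margin needs an observed difference below 10 − 6.6 = +3.4 points. Success at a 5-point margin needs one below 5 − 6.6 = −1.6 points. Every result between −1.6 and +3.4 points, exact equality included, passes under one reading and fails under the other.

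**The case against.** The strongest reply is that 0.05 is a drafting slip, perhaps the alpha value repeated, and that the trial was sized on 10 points. Power is then 80% as stated and nothing has been lost. That is quite possible, and for this reason the 34% must be read as conditional on 5 points being the real margin. It does not dispose of the point: the published margin would still be wrong, and nothing in the article identifies it as a slip.

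It can also be said that 10 points is not the only route to 249. A margin of 0.05 with a true 2-cycle rate of about 23.2% gives about 249, and a margin of 0.15 with about 32.7% gives about 250. The arithmetic is right. But the first assumes that 2 cycles are about 4.7 points better, against a text that anticipates an increase, and the second uses a margin found nowhere in the article. So 10 points remains an inference, though much the most natural one.

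Two further reservations stand. The 10% sentence does not say whether it is an expectation or a tolerance, or whether it is absolute or relative. And the sidedness of alpha is often left to an analysis plan, which is not shown here, so the one-sided 0.025 rows are sensitivity figures and not a separate criticism. Neither reservation brings a 5-point margin near 80% power at 249 per group with equal or worse 2-cycle rates.

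**Conclusion.** The concern holds. The margin as printed has no meaning for this endpoint. On the only usable reading of 0.05, an absolute difference, it is incompatible with 249 per group and 80% power: it needs 995 per group, and 249 give 34%. The size matches a 10-point margin.

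These figures rest on 27.9% pTRG3 in both arms, a one-sided alpha of 0.05 and the normal approximation, the same conditions that reproduce the plan's 249. What is established is that the margin, power and sample size contradict one another; a true loss of power follows only if 5 points was intended. Because the margin determines whether the trial succeeds, this must be corrected. Confidence is high.

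**What to change.** First retrieve the original calculation file and any dated protocol record, and establish which margin was prespecified. Do this, and record it, before anyone sees pTRG3 by arm.

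- **If 10 points is confirmed:** remove the hazard ratio label and the 0.05. State that the margin is an absolute difference of 0.10 in the proportion with pTRG3 (2 cycles minus 4 cycles), calculated with 27.9% in both arms, one-sided alpha 0.05 and 80% power. If a two-sided 95% confidence interval will be the criterion, restate power as 70%, or plan 316 evaluable per group.
- **If 5 points was intended:** state it as an absolute difference and either restate power as about 34% at one-sided 0.05 or resize to 995 evaluable per group.

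In either case say what the 10% sentence means (absolute or relative, expectation or margin) and use the same margin in the protocol, the registry entry and the analysis plan.

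The change to the text is about one sentence. If it counts as substantive, the Protocol amendments section requires review board approval and a registry update. No extra patients are needed if 10 points at one-sided 0.05 is confirmed or the lower power is accepted. Keeping 80% power at 5 points would need roughly four times the evaluable patients. The price of the first two courses is a stated margin or power that may look less favourable.
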